### Methods to Protect from Bias

Our study drug kits will contain active ketorolac and normal saline placebo (labelled as ketorolac) with instructions on dosing as per the randomization schedule. Ketorolac is identical to a normal saline placebo in appearance, consistency, and smell. Vials will contain clear liquid ketorolac 30 mg/ml or normal saline placebo ketorolac 30 mg/ml. Vials will be stored in consecutively numbered study drug kits according to the randomization schedule generated by the McMaster Children’s Hospital research pharmacy. The double-dummy design will ensure blinding of the research nurse drawing up and administering the drug. Bedside physicians and nurses, participants, and their families, investigators, research nurses, and clinical research assistants will all be masked to prevent bias in trial procedures and outcome assessment. Once participants are randomized, we will restrict all other pharmacologic analgesic cointerventions except acetaminophen and rescue therapy. Unblinding will not be permitted under any circumstances, as all participants will receive ketorolac and knowledge of the specific dose would not alter clinical management. Other medications that may be part of the patient’s treatment plan, such as antiemetics, antibiotics, or antihistamines, can be coadministered. Because the primary outcome is based on a self-reported pain scale, the semistructured survey will be conducted only after outcome assessments are completed. Research assistants can complete the semistructured survey after the 6-hour outcome assessment or, if the patient is discharged, within 7 days by phone or electronically. The trial is registered on clinicaltrials.gov (NCT05641363) [30].

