### Duration of Treatment and Follow-Up

Ketorolac and a placebo can be given as an IV slow push over 5 minutes with or without a drug pump. Only a single dose will be administered as part of the trial. The effects on pain will be monitored by obtaining baseline pain scores with the vNRS and at times 30, 60, 90, 120 minutes, and at 6 hours if they are still in the hospital. At follow-up, ED and inpatient chart reviews will be completed to determine results of investigations, AEs, total doses of opioids administered in morphine equivalents/kg, all types of NSAIDs administered, dose and frequency for each and the final diagnosis assigned. The survey will be completed within 7 to 14 days once all clinical outcomes are completed (6 hours postintervention).

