#### Secondary Endpoints

Secondary endpoints include the following:

vNRS score at 30, 90, and 120 minutes as well as 6 hours post administration.Proportion of participants who achieve the 2-point vNRS MID pain score reduction at 60 and 120 minutes.Proportion of participants who change the severity of their baseline pain category at all time points (mild = 0 to 3, moderate = 4 to 6, severe ≥7 on the vNRS)[24].Time to effective analgesia (ie, time at which a vNRS <3 is achieved postintervention).Proportion of participants requiring any rescue analgesia in each trial arm.Total amount administered as measured by morphine equivalent mg/kg within 8 hours of intervention.

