#### Safety Outcomes

Safety outcomes include the following:

The proportion of children experiencing any AEs, as reported by caregivers or clinical staff, will be recorded in accordance with the CONSORT Harms checklist [31]. We will solicit specific expected AEs that we found from our SR [32] to be commonly reported with NSAIDs, such as gastric pain. In addition, we will have open-ended questions to collect information on any additional unexpected AEs.Frequency of each specific AE (eg, nausea and vomiting). Time frame is 8 hours post drug administration.

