**Secondary outcomes**											
		**Efficacy**									
			Pain relief at all time points		Between group differences in pain score at all study time points at 30, 90 and120 minutes		Low dose will be noninferior to standard dose at all time points.		GEE^e^: adjusted for baseline pain scores		
			Pain relief by the MID		Proportion who achieves a 2-point vNRS reduction at 60 and 120 minutes		Low dose will be noninferior to standard dose ketorolac regimens in reducing pain by the 2-point MID^f^ on vNRS		Regression analysis		
			Pain category change		Proportion of participants who change their baseline pain category at all time points (mild 1 to 3, moderate 4 to 6, severe ≥7 on vNRS)		No difference between low dose and standard dose ketorolac in pain category change at all time points		Regression analysis		
			Time to achieve mild or no pain level		Time to effective analgesia as measured by the time when vNRS of <3 is achieved		No difference between all ketorolac dosing arms.		Cox regression analysis		
			Rescue analgesia		Proportion of participants requiring any additional analgesia in each trial arm		No difference between all ketorolac dosing arms		Regression analysis		
			Opioid sparring		Total amount of opioid administered within 8 hours of intervention		No difference between all ketorolac dosing arms		Regression analysis		

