### Trial Day-to-Day Operations

A study coordinator with experience in Health Canada drug trials will work with principal investigators ([name]). Clinical Research Assistants and research nurses will be available to recruit from 8 AM to 9 PM. We will present the study to staff physicians in the Pediatric ED, General Pediatrics, and Pediatric Surgery so they are aware of the study eligibility criteria and how to contact the study team members. Our research nurse will perform daily rounds in the ED and on the wards during clinical rounds to ask and remind the clinical team of any potential participants. The clinical team will ask potential participants if they would like to be approached by research personnel since they may be eligible for the KETODOSE trial. If the patients agree, they will be approached by research staff to check eligibility. Eligibility will then be confirmed with the treating physician or principal investigators, or both. If confirmed, the details of the study will be discussed with the patient and caregiver.

Children and caregivers will be consented and assented for participation in the trial, including the follow-up survey. Once caregivers’ consent and participants’ assent, the research nurse will obtain the drug kit from the ED drug dispensing machine and assign them the drug kit with the smallest subsequent number. Data will be prospectively collected on baseline characteristics, including age, sex, gender, baseline pain severity (vNRS), type of pain, location, and duration of pain and associated symptoms. Following randomization, the study drug kit containing the study drug vials with information on dosing will be administered to the patient by the research nurse or bedside nurse with the clinical research assistant’s help. Each patient will receive a single dose of IV ketorolac and 2 doses of normal saline as outlined in the intervention section above. Time 0 (baseline) will be considered the time at which study drug administration has been completed. Pain assessments will be conducted at 30-, 60-, 90-, and 120-minute intervals following study drug administration. A chart review will be performed approximately one week after the index visit to identify any return visits to the ED and document the reasons for representation, as well as abstract all data regarding other analgesia administered during the enrollment visit.

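### Adverse events and opioid use are 8-hour endpoints, but clinical outcomes are said to end at 6 hours and no described contact covers discharge to 8 hours

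*Protocol article*

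**What the plan says.** **Windows.** For specific adverse events, Safety Outcomes states: "Time frame is 8 hours post drug administration". The any-event item in the same list has no separate window. The opioid endpoint under Secondary Endpoints is "Total amount administered as measured by morphine equivalent mg/kg within 8 hours of intervention", and Table 1 agrees: "Total amount of opioid administered within 8 hours of intervention". Against these, Duration of Treatment and Follow-Up states: "The survey will be completed within 7 to 14 days once all clinical outcomes are completed (6 hours postintervention").

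**Observation.** Pain is scored at 30, 60, 90 and 120 minutes without condition, and then "at 6 hours if they are still in the hospital". Early discharge is foreseen: Methods to Protect from Bias says "Research assistants can complete the semistructured survey after the 6-hour outcome assessment or, if the patient is discharged, within 7 days by phone or electronically".

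**Sources.** Duration of Treatment and Follow-Up takes adverse events and opioid doses from emergency department and inpatient charts. Trial Day-to-Day Operations adds a chart review at about one week, which looks for return emergency visits and their reasons and will "abstract all data regarding other analgesia administered during the enrollment visit". Safety Outcomes also allows events reported by caregivers or clinical staff, with a solicited list and open-ended questions, but gives no time for asking them.

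**Survey.** The Secondary Objective Analysis Plan keeps survey findings out of the primary and secondary outcome analyses.

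**The concern.** An 8-hour endpoint needs 8 hours of ascertainment in every child, or a rule for those without it. Here the stated end of clinical outcomes falls short of the window, and the main sources are tied to time in hospital. For a child who goes home after the 120-minute score, the nominal 8-hour result may in practice describe a shorter and variable period.

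This matters because Table 1 hypothesises fewer adverse events on low dose, and the Conclusions rest part of the trial's value on safer prescribing. Adverse events are analysed as present or absent by logistic regression, which takes no account of hours observed. Discharge happens after randomisation and could depend on pain relief, so the observed share of the window could differ between arms.

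**Working it through.** **1. The window conflict.** The endpoint window is 8 hours (Safety Outcomes, Secondary Endpoints, Table 1). The stated completion of all clinical outcomes is 6 hours (Duration of Treatment and Follow-Up). The gap is 8 − 6 = 2 hours, or 2/8 = 25% of the window.

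**2. What covers a child discharged before 8 hours.**
- Chart review: covers time in hospital. It is retrospective, so it can reach 8 hours for a child who stays.
- Abstraction of other analgesia: enrolment visit only. Doses taken at home have no stated source.
- One-week chart review: finds events that led to a return emergency visit, not milder events at home.
- Solicited and caregiver-reported events: could cover the gap, but no contact time is given.
- Caregiver survey: the one described contact after discharge. It covers perceptions of adverse events, is separated from the outcome analyses, and is timed differently in different places (within 7 days if discharged, against 7 to 14 days).

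**3. Illustration of scale.** The documents give no discharge times or adverse event rates, so every input in this step is an assumption. Suppose events after discharge are not captured and count as none. Then

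observed risk = true risk × (1 − d × f),

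where d is the share discharged early and f is the share of their events that fall after discharge. For a true 8-hour risk of 20%:
- d = 0.3, f = 0.25: 0.20 × 0.925 = 18.5%
- d = 0.6, f = 0.5: 0.20 × 0.70 = 14.0%
- d = 0.9, f = 0.5: 0.20 × 0.55 = 11.0%

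Between arms, with equal true risks of 20%, f = 0.5, and early discharge of 50% and 80%: 0.20 × 0.75 = 15% against 0.20 × 0.60 = 12%, a spurious 3-point difference.

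With true risks of 20% (standard) and 15% (low dose), constant risk over time, and discharge at 3 hours (f = 5/8):

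| Early discharge, standard / low dose | Observed, standard | Observed, low dose | Difference |
|---|---|---|---|
| 60% / 45% | 0.20 × 0.625 = 12.5% | 0.15 × 0.719 = 10.8% | 1.7 points |
| 50% / 50% | 0.20 × 0.6875 = 13.75% | 0.15 × 0.6875 = 10.3% | 3.4 points |
| 45% / 60% | 0.20 × 0.719 = 14.4% | 0.15 × 0.625 = 9.4% | 5.0 points |

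The true difference is 5 points and the true ratio 1.33. The first row pulls the ratio down to 1.16, the second leaves it unchanged, and the third raises it to 1.53. The direction depends wholly on the assumed discharge pattern.

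**4. What is untouched.** The sample size rests on the 60-minute score. SD 1.5, difference 0.2, margin 1.0, one-sided 0.025 and 80% power give 56 per group by the normal approximation. A t-based calculation gives power of 0.799 at 56 and 0.806 at 57, which reproduces the stated 57; 57/0.95 = 60 after the 5% allowance.

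**The case against.** A reader might infer that a child discharged early is scored as free of both adverse events and opioid use for the unobserved hours. The documents do not say so. No scoring rule is given, and such a rule commonly sits in an analysis plan or case report form that is not shown. For adverse events the inference is weak: caregiver reports and solicited questions are planned, return visits are checked, and the enrolment-visit limit applies to analgesia only. For opioids it is more plausible, because a total summed from charts counts nothing after discharge. Yet if the endpoint means opioid given in hospital, that zero is a true value. The article does not say which is meant.

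The 6-hour remark sits in a sentence about survey timing and may be a loose reference to the last pain score. That is a fair reading, but the words cover all clinical outcomes, and even the generous reading supplies no source for hours at home.

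The trial is also small for adverse events. At 60 per arm, 20% against 15% has a standard error of √(0.20 × 0.80/60 + 0.15 × 0.85/60) = 0.069 and power of about 11%, so attenuation would seldom change a significance test. That stands, but the estimates and intervals will still be reported as 8-hour figures. Finally, the article reports 170 of 180 children enrolled, so new questions can reach only about 10.

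**Conclusion.** The concern holds in limited form. The 6-hour and 8-hour statements conflict, and no described contact covers discharge to 8 hours. The 8-hour adverse event and opioid figures may therefore under-count events after discharge. The size is unknown: the illustrations rest on assumed discharge shares, discharge times and event rates, and on the assumption that uncaptured events count as none. A reader might also infer that the bias works against the hypothesis of fewer events on low dose. The documents do not support that, since they give no discharge pattern by arm and the illustrated effect changes direction with the pattern assumed. Only secondary and safety endpoints are touched; the 60-minute primary endpoint and the sample size are not. This is a cheap improvement, not a threat to the main result.

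**What to change.** 1. Reconcile the 6-hour and 8-hour statements, and state the source of adverse event and opioid data between discharge and 8 hours.
2. For remaining participants discharged before 8 hours, use the already planned caregiver contact to ask the solicited adverse event list and any analgesics taken up to 8 hours. Record the answers as outcome data, separate from the attitude survey, so that the exclusion of survey findings does not remove them. Give that contact one consistent time frame.
3. If home use is not ascertained, label the opioid endpoint as in-hospital administration.
4. Do not count unobserved hours as event-free.
5. Before unblinding, add an analysis of adverse events and opioid use over 0–120 minutes, when all children are scheduled to be observed, alongside the 8-hour result. Apply it to every child. Using it only for those with incomplete follow-up would make each child's window depend on discharge and bring the problem back.

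The cost is wording, a few questions at an existing contact and one extra analysis. The drawbacks are recall error, few children left to benefit from the questions, and a common window that captures fewer events. It also covers little of the rescue period, since the Interventions section allows rescue analgesia only from 60 minutes, which leaves one hour of it.

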### Primary and Secondary Outcome Measures

#### Primary Objective Endpoint

Between each low-dose ketorolac group (B1 and B2) and the standard group (A) mean differences in pain as measured on vNRS at 60 minutes. We selected 60 minutes postadministration as the time of our primary outcome assessment after careful consideration and in discussion with our parent and youth collaborators and our clinical pharmacologist coinvestigator. This time point (1) allows children to settle from anxiety associated with IV start, which may confound pain assessment; (2) is an acceptable time point for fair assessment of the analgesic effects of the study drug, with a good balance between onset and peak effect for ketorolac; and (3) is a reasonable timeframe for patients to expect relief from vigorous pain.

#### Secondary Endpoints

Secondary endpoints include the following:

vNRS score at 30, 90, and 120 minutes as well as 6 hours post administration.Proportion of participants who achieve the 2-point vNRS MID pain score reduction at 60 and 120 minutes.Proportion of participants who change the severity of their baseline pain category at all time points (mild = 0 to 3, moderate = 4 to 6, severe ≥7 on the vNRS)[24].Time to effective analgesia (ie, time at which a vNRS <3 is achieved postintervention).Proportion of participants requiring any rescue analgesia in each trial arm.Total amount administered as measured by morphine equivalent mg/kg within 8 hours of intervention.

#### Safety Outcomes

Safety outcomes include the following:

The proportion of children experiencing any AEs, as reported by caregivers or clinical staff, will be recorded in accordance with the CONSORT Harms checklist [31]. We will solicit specific expected AEs that we found from our SR [32] to be commonly reported with NSAIDs, such as gastric pain. In addition, we will have open-ended questions to collect information on any additional unexpected AEs.Frequency of each specific AE (eg, nausea and vomiting). Time frame is 8 hours post drug administration.

#### Secondary Objective

Semistructured survey with baseline demographics, closed-ended questions (7-point Likert scale), and open-ended questions will be collated, summarized, and analyzed by subgroup (age and gender). Time frame for completion is 7-14 days post randomization.

### Outcome Measurement Tools

We will measure pain using the 11-point vNRS, a validated self-reported acute pain scale for which an anchor-based MID has been established (2 points). The vNRS has demonstrated strong convergent validity, known-groups validity, responsivity, and test-retest reliability in children 6-17 years old with acute pain and in the emergency setting [24,25]. It is rapidly administered by asking, “On a scale of 0 to 10, where 0 means no pain and 10 means the worst pain, how much pain do you have right now?” In a recent systematic review of all acute pain scales for children, the vNRS was the only one to receive a strong recommendation for use in children aged ≥6 years [23]. A phone or electronic questionnaire will be administered after all pain assessments are completed within 7-14 days of enrollment, either in person or by phone or email to assess (1) caregiver knowledge and attitudes toward widely available analgesics; (2) attitudes and fears associated with IV analgesics; and (3) caregiver perceptions of dosing of analgesics as well as AEs associated with them (see Multimedia Appendix 4).

### Sample Size Calculations

Based on adult studies [5,9,11,33], we estimated an SD of 1.5 in each group and a mean difference of 0.2. The noninferiority margin of 1.0 is carefully selected to ensure that a rejection of the null hypothesis would: (1) include the effect size that standard dose ketorolac has historically displayed when compared to placebo (relative risk of achieving 50% pain reduction compared to placebo 2.81, 95% CI [1.8-4.4] with number needed to treat of 2.4, 95% CI [1.8, 3.7]), [10] and (2) exclude clinically important levels of inferiority by keeping our margin at 50% of the known MID of 2.0 on the vNRS, ensuring ethical and relevant clinical application. A statistician [name] using nQuery Software (Insightful Science), calculated a total sample size of 171 participants (57/group), which would allow us to test our noninferiority hypothesis using a one-sided alpha of 0.025, 80% power, and a noninferiority margin (Δ) of 1.0. Since our primary outcome is short-term (60 minutes) and we are testing a single dose of ketorolac, we expect very few patients withdrawals or loss to follow-up. However, we will increase our sample size by 5%, to 60 per group (total 180 participants), to account for any unanticipated withdrawals.

### Analysis Plan

#### (A) Primary Objective Analysis Plan

Data will be described in terms of mean (SD) or 95% confidence limits for normally distributed data and frequency (percentage) in the case of categorical data. The primary endpoint is the difference between the mean reduction in pain scores between each of the low-dose groups (B1, B2) and the standard-dose group (A) 60 minutes post intervention. The primary analysis will include all participants randomized based on the intention to treat analysis and a sensitivity per-protocol analysis will also be performed. A priori, the primary analysis will be adjusted for baseline pain scores using the analysis of covariance (ANCOVA)*.* Generalized estimating equations will be used to examine the impact of baseline pain score on vNRS outcomes across the entire time frame. Noninferiority would be shown if the lower limit of the 95% CI for the between group (groups B1vs A or B2 vs A) differences in the primary endpoint is >1.0. If >5% [34] of our vNRS scores are missing within 120 minutes, we will use multiple imputation to create 5 datasets wherein any missing pain data will be imputed with the Markov chain Monte Carlo method. For secondary endpoints, we will describe those outcomes using descriptive statistics and perform a linear (continuous), logistic, or ordinal regression (categorical or ordinal). If both low-dose strategies are shown to be noninferior to standard dose, we will conduct an exploratory analysis to see if one low-dosing strategy is superior to the other (group B1 vs B2). This will be conducted using ANCOVA to adjust for baseline pain scores and superiority will be determined by a difference that is defined by the MID of 2.0 on the 11-point vNRS. All analyses will be conducted in a blinded fashion. The research pharmacist will provide the trial statistician with anonymized group allocation codes, without revealing the dosing strategies associated with each group. The group identities will remain blinded to the statistician until the first draft of the manuscript with results has been completed. All analyses will be done using SAS (version 9.4; SAS Inc).

AEs profile analysis: the proportion of children experiencing any AEs as reported by caregivers or health care providers will be compared between groups using logistic regression and presented with their corresponding binomial 95% 2-sided CI. The analysis will evaluate the presence or absence of AEs in each group, such as nausea, epigastric pain, or dyspepsia.

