**Methods:**

The KETODOSE trial is a single-center, randomized, double-blind, double-dummy, noninferiority trial conducted at McMaster Children’s Hospital. Eligible participants aged 6 to <18 years with vigorous pain (vNRS >4) are randomized in a 1:1:1 ratio to standard dosing or one of 2 low-dose ketorolac regimens. Study drugs are administered via intravenous push over 5 minutes. Pain scores are assessed at baseline, 30, 60, 90, and 120 minutes. The primary endpoint is the mean change in vNRS score at 60 minutes. Secondary outcomes include pain scores at other time points, time to effective analgesia, rescue analgesia requirements, opioid consumption, and adverse events. Caregiver perceptions regarding analgesic use are evaluated using a mixed-methods semistructured survey. A sample size of 180 participants (60 per group) provides 80% power to detect noninferiority within a margin of 1.0 on the vNRS, assuming an SD of 1.5. Intention-to-treat and per-protocol analyses will be performed.

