**Primary efficacy outcome^a^**											
		Pain relief		Pain level as reported by participants on an 11-point vNRS^b^ score at 60 minutes post administration of trial drugs.		Ketorolac given at 0.5 mg/kg/dose up to 10 mg or at 0.25 mg/kg/dose up to 30 mg will be noninferior to standard dose ketorolac		Intention to treat analysis using ANCOVA^c^			

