**Sensitivity analysis**											
		Per-protocol analysis		Completed for the Primary and Safety outcomes		The primary intention to treat analysis results will remain robust		ANCOVA Regression analysis			

^a^Sample size calculation is based on the primary efficacy outcome.

^b^vNRS: 11-point verbal Numerical Rating Scale.

^c^ANCOVA: analysis of covariance

^d^AEs: adverse events.

^e^GEE: generalized estimating equations.

^f^MID: minimal important difference.

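### The noninferiority decision is tied to intention-to-treat, and the planned per-protocol analysis has no say in it; the resulting risk of a false claim is modest but cheap to close

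*Protocol article*

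**What the plan says.** The analysis plan for the primary objective fixes the order of the two sets: everyone randomized is analysed by intention-to-treat as the primary analysis, and "a sensitivity per-protocol analysis will also be performed". Table 1 gives the primary efficacy analysis as "Intention to treat analysis using ANCOVA" and places per-protocol in its sensitivity block. There its scope is "Completed for the Primary and Safety outcomes" and the stated expectation is "The primary intention to treat analysis results will remain robust".

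The decision rule is a single confidence-interval criterion, beginning "Noninferiority would be shown if the lower limit of the 95% CI for the between group". That sentence names no analysis set, but it follows directly on the definition of the primary analysis as intention-to-treat. The abstract says only "Intention-to-treat and per-protocol analyses will be performed", with no ranking and no joint rule. The sample size section sets the error rate: "using a one-sided alpha of 0.025, 80% power, and a noninferiority margin (Δ) of 1.0".

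**The concern.** In a superiority trial, deviations that pull the arms together make a false claim less likely. In a noninferiority trial they make it more likely, because a shrunken difference sits further inside the margin. The article describes routes by which this could happen:

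- Each child receives one active and two saline injections from identical-looking vials, at three different weight-based and capped amounts (Interventions; Methods to Protect from Bias). A mix-up of vial and volume could turn one arm's dose into another's.
- Rescue is foreseen from 60 minutes, which is also the time of the primary score (Interventions). Analgesia given before that, if commoner in a low-dose arm, would lower that arm's 60-minute score.
- Recent NSAID use was the main recruitment obstacle (Results). A child enrolled in error after an NSAID stays in the intention-to-treat set.

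Under the rule as written, a per-protocol result that misses the margin would neither block nor formally qualify the claim. The Discussion says that the margin ensures any declaration of noninferiority reflects comparable effectiveness, and the Conclusions expect the result to inform prescribing. The decision rule should be able to carry that weight for both comparisons (B1 against A, B2 against A).

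**Working it through.** **Inputs.** From Sample Size Calculations: SD 1.5, expected true difference 0.2, margin 1.0, one-sided alpha 0.025, power 80%, 57 per group raised by 5% to 60. The article gives no deviation rate, so the fraction f of the dose contrast that is lost is an assumption, shown as a range. The margin is read as a 1.0-point shortfall in the low-dose arm.

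**1. The plan's own figure.** n = 2 × SD² × (1.960 + 0.842)² / (1.0 − 0.2)² = 2 × 2.25 × 7.85 / 0.64 = 55.2, so 56 per group by the normal approximation. With the noncentral t, power is 79.9% at 56 and 80.6% at 57, so 57 is reproduced. 57 × 1.05 = 59.85, so 60.

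**2. Error from intention-to-treat under dilution.** SE = 1.5 × √(2/60) = 0.274. Let the true difference be exactly 1.0, the null boundary. If a fraction f of the contrast is lost, the expected intention-to-treat difference is 1.0 × (1 − f), and the chance of a false claim is 1 − Φ(1.96 − f/0.274).

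| f (assumed) | f/0.274 | False claim |
|---|---|---|
| 0% | 0 | 2.5% |
| 2% | 0.07 | 3.0% |
| 5% | 0.18 | 3.8% |
| 10% | 0.37 | 5.5% |
| 20% | 0.73 | 10.9% |

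**3. Error with both sets required.** Take a per-protocol set of 57 per group (5% excluded) or 54 (10% excluded). The correlation between the two test statistics is √(57/60) = 0.975 or √(54/60) = 0.949. Assume that the excluded children show no contrast and that the exclusions are unrelated to outcome. Simulated with t tests, the intention-to-treat error is about 3.7% at 5% and 5.3% at 10%. This is slightly below the table because mixing children with and without a contrast widens the SD a little. The joint rule brings the error to about 2.3% in both cases.

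**4. Power with both sets required**, at a true difference of 0.2. Per-protocol alone gives 80.6% at 57 per group and 78.4% at 54 (noncentral t). Joint power must be lower than that: about 79% and 77% by simulation, against 82–83% for intention-to-treat alone with 60 per group. Holding 57 per group in the per-protocol set at 10% exclusions would need 57/0.90 = 63.3, so 64 per group or 192 in total.

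**The case against.** **The safeguard is largely there.** A reader might infer that the trial relies on intention-to-treat and nothing else. That goes too far. A per-protocol analysis of the primary outcome is prespecified in the abstract, the analysis plan and Table 1, so a discordant result would be produced and seen. What is missing is its role in the decision. Nor is this simply detail left to a statistical analysis plan: the article itself ranks the sets and states one criterion. The exact definition of the per-protocol set may well be in that plan, and its absence here is not counted.

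**Deviations are probably few.** The trial gives one staff-administered dose from numbered kits, scores the outcome at 60 minutes, expects very few withdrawals and monitors dosing compliance. This stands, and it points to the upper rows of the table. A reader might take 10.9% as the expected error. That figure needs a fifth of the contrast erased and a true difference exactly at the margin, whereas the plan assumes 0.2. The documents do not support it as a likely value.

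**Not every deviation dilutes.** This also stands. If active drug fails to reach children in a low-dose arm only, the difference widens and intention-to-treat becomes conservative. The direction depends on which arm deviates.

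**Per-protocol is not an unbiased remedy.** This stands too. It gives up the protection of randomization, and it would not remove dilution from acetaminophen, which is permitted. If children with early analgesia are excluded and they are mostly low-dose failures, the per-protocol set itself moves towards noninferiority. Adding it as a second condition can only lower the false-claim rate, but it would protect little against that route.

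**Conclusion.** The point holds in a limited form. The article ties noninferiority to intention-to-treat and gives the per-protocol analysis no part in the decision, so deviations that shrink the contrast could support a false claim. At plausible rates the inflation is modest: about 3.0% at 2%, 3.8% at 5% and 5.5% at 10%, against a nominal 2.5% for each comparison. This rests on assumed dilution rates, a true difference at the margin, the planning SD of 1.5 and deviations that act towards equality. If baseline adjustment brings the residual SD below 1.5, both the power and the inflation for a given f are somewhat larger. The matter should be settled in the decision rule before the group codes are released; it does not undermine the design.

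**What to change.** State that noninferiority is declared for a low-dose arm only if the confidence limit meets the margin in both the intention-to-treat and the per-protocol sets. If only one set meets it, report that noninferiority was not shown for that arm and give both results.

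Fix the list of per-protocol exclusions before the research pharmacist passes the anonymized group codes to the statistician. Deviations are already documented under Trial Monitoring, so the information should be to hand.

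Do not let analgesia given before the 60-minute score by itself remove a child from the per-protocol set. Examine its influence in a separate, prespecified sensitivity analysis.

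The cost is wording plus a small loss of power: joint power of about 79% with 5% exclusions and about 77% with 10%, slightly below the stated 80%. The sample size stays at 180, of whom 170 had been enrolled when the article was submitted. The shortfall should be stated openly.
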